### Strengths of This Study

The strengths of the study can be summarized as follows. This study uses a prospective design to assess a new strategy for managing the pancreatic stump during distal pancreatectomy. The new strategy will provide a sufficiently high pancreatic duct burst pressure while preserving partial blood supply to the pancreatic stump.

### Limitations

One of the primary limitations of this study is its nonrandomized controlled design. Since this study investigates a novel pancreatic stump management technique that has not yet undergone large-scale clinical validation, the institutional ethics committee recommended an enrollment approach based on patient choice to ensure patient autonomy. Furthermore, the involvement of 2 distinct surgical techniques precluded blinding of the investigators. These factors may introduce performance and detection biases into the study. On the basis of the findings of this investigation, the research team will evaluate the need for subsequent randomized controlled clinical trials to address these methodological constraints. The relatively small sample size is another limitation of this study. The inherent variability among the included cases may prevent confirmation of the study hypothesis. We will make a data-driven decision regarding potential sample size expansion.

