##### Alternative Hypothesis

The rate of POPF in patients who undergo pancreatic stump ligation is lesser than that using other closure techniques.

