#### Sample Size Calculation

Based on published clinical studies on the incidence of pancreatic fistula [6-8] using other closure techniques, the incidence of POPF was set at 40%. On the basis of the results of previous animal experiments, the expected incidence of POPF in the ligation strategy is 5%. Using the formula *n = 2p̅q̅(Z_α_+Z_β_)^2^/(p1-p2)^2^* for sample size calculation with the probability of type I error of .05 and the statistical power of .90, we estimated that 30 participants should be included in each group.

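### An unspecified data-driven option to enlarge the sample conflicts with the fixed 30 per group, so the stated type I error of .05 is not guaranteed

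*Protocol article*

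**What the plan says.** Under Sample Size Calculation, the article assumes postoperative pancreatic fistula (POPF) rates of 40% with other closure techniques and 5% with ligation. It takes a "probability of type I error of .05 and the statistical power of .90, we estimated that 30 participants should be included in each group".

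Three places treat that number as final. The Abstract (Methods) and Group Allocation both stop recruitment to a group once its predefined size is reached. Results says that recruitment ends when the estimated sample size is achieved, around September 2025.

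The Limitations section takes a different line. It names the small sample as a limitation and continues: "The inherent variability among the included cases may prevent confirmation of the study hypothesis". The next sentence is: "We will make a data-driven decision regarding potential sample size expansion". The same paragraph says that the investigators could not be blinded.

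Statistical Methods describes no interim analysis, re-estimation rule, maximum sample size or adjustment of the test. The predefined criteria mentioned in the Discussion (Overview) concern adverse events and withdrawal or stopping, not sample size.

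**The concern.** A type I error of .05 for one test at a fixed sample size holds only if that size does not depend on the comparison being tested. The Limitations sentence removes that condition without putting a rule in its place. It follows a remark about failing to confirm the hypothesis, and nothing stated keeps results by group from those who would decide. The text therefore permits an uncontrolled second look.

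POPF is a primary end point and the only one with a stated hypothesis. If patients were added after a disappointing comparison and the enlarged data set were tested again at .05, a positive result could not be read at the stated level. The estimated difference could also be biased, because the size of the trial would depend on the result.

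Separately, the article does not agree with itself on whether recruitment stops at 30 per group.

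**Working it through.** **1. Reproduce the planned size.** Inputs from Sample Size Calculation: p1 = 0.40, p2 = 0.05, alpha .05, power .90. The article's formula is n = 2·p̄·q̄·(Zα + Zβ)² / (p1 − p2)², with p̄ = (0.40 + 0.05)/2 = 0.225 and q̄ = 0.775.

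- Two-sided: 2 × 0.225 × 0.775 × (1.960 + 1.282)² / 0.35² = 29.91, so 30. This matches.
- One-sided: with 1.645 in place of 1.960 the result is 24.38, so 25. This does not match.

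Sidedness is not stated and the alternative is directional ("The rate of POPF in patients who undergo pancreatic stump ligation is lesser than that using other closure techniques"). The planned 30 nevertheless rests on a two-sided .05, so that level is used below.

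**2. Scenario A (assumed): enlarge whenever the first test is not significant.** Test at 30 per group at two-sided .05. If not significant, enlarge to n2 per group and retest all data at .05. Under the null hypothesis the two z statistics are approximately bivariate normal with correlation √(30/n2), and

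overall error = 1 − P(|z1| < 1.96 and |z2| < 1.96).

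| n2 per group | Correlation | Overall two-sided error | Error in favour of ligation |
|---|---|---|---|
| 40 | 0.866 | 7.3% | 3.7% |
| 45 | 0.816 | 7.7% | 3.8% |
| 60 | 0.707 | 8.3% | 4.2% |
| 90 | 0.577 | 8.8% | 4.4% |

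With a single test at 30 per group, the last two columns would be 5% and 2.5%.

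**3. Exact check of scenario A.** Binomial enumeration with an uncorrected chi-square test at a common POPF rate of 40% gives 4.9% for the single test at 30 per group, 7.5% after enlarging to 45 and 8.3% after enlarging to 60. At a common rate of 22.5% the two enlarged figures are 8.0% and 8.4%.

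**4. Scenario B (assumed): enlarge to 60 per group only if the first z lies between 1 and 1.96 in favour of ligation.**

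- Chance of landing in that zone under the null: 0.1587 − 0.0250 = 0.1337.
- Chance of landing there and then rejecting at the second test: 0.0118.
- Conditional on being in the zone: 0.0118 / 0.1337 = 8.8%.
- Overall two-sided error: 0.0500 + 0.0118 = 6.2%.

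The 6.2% is the trial's error rate. The 8.8% applies only once the first result is already in the zone.

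**5. Cases with little or no harm.**

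- If only the POPF rate with groups combined guides the decision, inflation is negligible.
- With Fisher's exact test under scenario A at a common rate of 40%, the error goes from 2.6% (single test at 30) to 4.4% (45) and 4.9% (60). At 22.5% it goes from 2.4% to 4.0% and 4.5%. It stays under .05 only because the test is conservative.

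**6. Level that would hold .05.** Two looks at 30 and 60 per group with an equal boundary need |z| > 2.178 at each, a two-sided level of 0.0294.

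**The case against.** The sentence says less than a reader might infer from it. It does not say that the first 60 patients will be tested, that a non-significant result triggers enlargement, that all data will be retested at .05, or that results by group will be used. A decision guided by the pooled POPF rate would also be data-driven and would do almost no harm. Lack of blinding makes a comparative look possible; it does not show that one is planned. The preceding sentence makes that reading plausible without establishing it.

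The test is open too. Statistical Analysis names none for comparing the groups and the Abstract refers only to appropriate tests, so the chi-square figures rest on an assumption. For a directional claim, the relevant error under scenario A at 60 per group goes from 2.5% to 4.2%.

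The sentence also stands in the Discussion, while the operative sections fix the size. This is a condensed article, and details of an adaptive rule may be in a full protocol or analysis plan that is not shown. Finally, in a 60-patient study with allocation by patient choice, confounding threatens the inference more than a few points of alpha.

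Most of this stands, and it limits the claim to an error rate that is not guaranteed. It does not remove the point. The article makes a positive, open-ended statement that contradicts its own recruitment rule, so this is more than missing detail. It commits to neither safeguard, pooled data or a conservative test. Confounding is a separate problem that enlargement would not cure.

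**Conclusion.** The point holds in a limited form. The option to enlarge the sample is unspecified, is tied in the text to possible failure to confirm the hypothesis, and is inconsistent with recruitment that stops at the predefined size. The .05 in the sample size calculation is therefore not guaranteed.

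The stronger statement, that .05 is certainly lost, is not supported, because no trigger, retest or review by group is described. The inflated figures are assumed scenarios: 7.3% to 8.8% if every non-significant first result leads to enlargement to between 40 and 90 per group and an unadjusted retest, and 6.2% overall under the narrower rule in scenario B. They rest on a two-sided .05 and, apart from the exact checks, on a normal approximation. Nothing in the article suggests repeated enlargements, so no larger figure is claimed. Under pooled-rate review, or in the cases computed for Fisher's exact test, the error stays near or below .05.

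**What to change.** **Preferred.** Delete the sentence on expansion from Limitations. State that the confirmatory analysis is that of the planned 60 patients and that any later patients form a separate study. Limitations already foresees possible later randomized trials.

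**If the option is to stay**, choose one of these and write it into Statistical Methods:

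- Base the decision only on the POPF rate with both groups combined, and fix a maximum sample size.
- Prespecify two analyses, at 30 and 60 per group, each tested at two-sided 0.0294.

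In either case state when the decision is made and who makes it, and bring the Abstract, Group Allocation, Results and Limitations into agreement on when recruitment stops.

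**Cost.** One sentence or a short amendment, and the loss of an informal option to continue. To be credible, the change has to be made before outcomes by group are reviewed. The two-analysis route also costs some power at the first look. On the article's assumptions and formula, √(30 × 0.35² / (2 × 0.225 × 0.775)) = 3.246; 3.246 − 2.178 = 1.068, or about 86% power at 30 per group. A single test at .05 gives 3.246 − 1.960 = 1.286, or about 90%.

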## Appendix

Multimedia Appendix 1 SPIRIT (Standard Protocol Items: Recommendations for Interventional Trials) checklist.

Multimedia Appendix 2 Informed consent form.

## Abbreviations

CTCAE: Common Terminology Criteria for Adverse Events
MPD: main pancreatic duct
POPF: postoperative pancreatic fistula
SPIRIT: Standard Protocol Items: Recommendations for Interventional Trials
